### ARMS Mobile App Intervention

ARMS is a hybrid mobile/IOS web-based app for contingency management designed to integrate with the electronic medical record of treatment programs, providing clinicians with an adjunctive treatment modality to (1) administer contingency management treatment to patients with AUD remotely, (2) access updated patient information that can be critical to the clinical management of AUD, and (3) communicate safely and directly with patients through the ARMS app. ARMS includes two separate interfaces: (1) a mobile/IOS interface to be used by patients and (2) a web-based application to be used by treatment providers.

### Patient Interface and Dashboard

The patient interface includes five features: (1) recording and submitting breathalyzer samples, (2) recording and submitting ecological momentary assessments (EMAs) on moods and executive function that may be pertinent to treatment, (3) reminders and messages, (4) redemption of rewards, and (5) a patient dashboard (see below for more details). To comply with the Health Insurance Portability and Accountability Act requirements, ARMS uses a user-protected login for access.

### Breathalyzer Sample Recording and Submission

A critical aspect of the contingency management component involves providing rewards contingent upon the objective verification of alcohol abstinence. In ARMS, the patient mobile interface syncs via Bluetooth with a BACtrack breathalyzer device, enabling the recording and submission of breathalyzer sample results from the BACtrack device to the ARMS app. The app prompts users, instructing them to place their face in the center of a square displayed on their phone screen while blowing into the breathalyzer. A photo is then captured to allow for facial recognition of the patient submitting the sample (ie, a full-face image is required to conduct the facial recognition). Immediately after the breathalyzer result is captured, the ARMS app presents both the breathalyzer result and the facial image and provides the patient the option to submit the breathalyzer result to their provider. If the patient agrees with the breathalyzer result and believes that the captured image will allow them to be identified, they can click on “submit” and the breathalyzer result will be uploaded onto a secure server accessible only by their treatment providers and the study researchers. If the patient does not agree with the breathalyzer result or believes that the photo will not allow for facial recognition, the option to submit another sample can be chosen.

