Once the modifications are made in response to the second wave of clinician feedback, ARMS will be evaluated primarily for efficacy but also for feasibility and patient usability through an A-B-A (or, “return-to-baseline”) completely within-subject experimental design. Following similar single subject-design studies conducted by our group [20,24], the two A phases will each last 2 weeks and the B phase will last 4 weeks, for a total study duration of 8 weeks. During all phases, participants will be asked to use the ARMS app to submit breathalyzer samples at 10 AM, 2 PM, and 8 PM each day. Submission of each sample should take less than 5 minutes. Participants will be prompted by their ARMS app to record and submit their breathalyzer samples at these predetermined times and will have a half-hour window following the prompt to submit each sample. During the A phases (control conditions), participants will earn US $2 in vouchers for every breathalyzer sample submitted during the predetermined period, independent of their sample results. Notably, this reward system will be in effect for both the first and second A phases. During the B phase (contingency management condition), vouchers will be provided contingent upon the submission of alcohol-negative breathalyzer samples—that is, breath alcohol content (BAC) = 0.00. Participants will begin by receiving vouchers worth US $2 per alcohol-negative breath sample submitted, with the value escalating by US $0.25 per alcohol-negative sample submission to a maximum value of US $3.50 per submission. Vouchers will be reset to US $2 per sample if a participant does not submit a sample in the predetermined period, if an alcohol-positive breath sample is submitted, or if the participant cannot be identified from the facial recognition photo (see details below).

At the end of the A-B-A experiment trial, the patients’ acceptability of ARMS will be evaluated with the System Usability Scale (SUS).

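### Patients see each breath result before choosing whether to upload it, and payment for a positive differs by phase, so the A-versus-B abstinence contrast can be biased toward B

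*Protocol article*

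**What the plan says.** **Capture of the reading** (Methods, Breathalyzer Sample Recording and Submission). The patient sees the result before deciding: "Immediately after the breathalyzer result is captured, the ARMS app presents both the breathalyzer result and the facial image". If the patient accepts both and submits, "the breathalyzer result will be uploaded onto a secure server accessible only by their treatment providers and the study researchers". The alternative branch opens "If the patient does not agree with the breathalyzer result or believes that the photo will not allow for facial recognition", and then "the option to submit another sample can be chosen". The article gives no limit on repeats and does not say whether a discarded reading is kept.

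**Payment** (Methods, Study Design). The same app and the same three daily prompts are used in all phases, and patients "will have a half-hour window following the prompt to submit each sample". In both A phases "participants will earn US $2 in vouchers for every breathalyzer sample submitted during the predetermined period, independent of their sample results". In phase B "vouchers will be provided contingent upon the submission of alcohol-negative breathalyzer samples". The B voucher starts at US $2, rises by US $0.25 per negative sample to a cap of US $3.50, and returns to US $2 "if a participant does not submit a sample in the predetermined period, if an alcohol-positive breath sample is submitted", or if the photo does not identify the patient.

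**Use of the result** (Methods, Outcomes). Feasibility is judged by whether ARMS significantly increases abstinence. Study Design describes the A-B-A experiment as primarily an efficacy evaluation. Self-reported drinking (ATFB) is an additional secondary outcome, and the proportion of breath samples submitted is an adherence outcome.

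**The concern.** The breath test is meant to be the objective measure of abstinence, yet the patient decides, knowing the result, whether it is sent. That would be a smaller problem if the incentive to send a positive were the same throughout. It is not: disclosure of a positive is paid in A and unpaid in B. Whether a positive reading reaches the data can therefore depend on both the outcome and the phase being compared.

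The A-B-A design offers no protection. The payment rule reverts in the second A phase, so a reporting artefact would revert with it. The resulting rise and fall is the pattern that would be read as a treatment effect, and the feasibility conclusion rests on it. If discarded readings are not stored, no later analysis rule can recover them.

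**Working it through.** The article gives no figure to reproduce on this point. The check takes the payoffs from its voucher schedule, then shows how each route acts when true drinking is identical in all phases.

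**Step 1. Voucher payoff after a positive reading (inputs from Study Design)**

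| Patient's choice | Phase A | Phase B |
|---|---|---|
| Submit the positive | US $2 | US $0, reset to US $2 |
| Submit nothing | US $0 | US $0, reset to US $2 |
| Replace by a negative repeat within the window | US $2 | current voucher (US $2 to US $3.50), no reset |

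- Withholding compared with submitting: A, 0 − 2 = −US $2; B, 0 − 0 = US $0.
- Replacing compared with submitting in A: 2 − 2 = US $0.
- Replacing compared with submitting in B, at the cap: the voucher of 3.50, plus the re-escalation loss avoided, 1.50 + 1.25 + 1.00 + 0.75 + 0.50 + 0.25 = 5.25. Total US $8.75.
- Replacing compared with submitting in B, with the voucher at US $2: 2.00, plus six later vouchers each US $0.25 higher (1.50). Total US $3.50.

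The two B totals assume that later samples are negative and that enough prompts remain to climb back to the cap.

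**Step 2. Withholding**

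Let p be the true share of positive prompts, equal in all phases, and r the submission rate of positives in B relative to A. Negatives are submitted at the same rate s in every phase, and in A positives are too. The values of p and r are assumptions.

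- Scoring submitted samples only: A gives 1 − p; B gives (1 − p) / [(1 − p) + p·r].
  - p = 0.20: A 80%. B at r = 0.6 is 0.80/0.92 = 87%; at r = 0.2 it is 0.80/0.84 = 95%. Spurious gain 7 to 15 points.
  - p = 0.30: A 70%. B at r = 0.6 is 0.70/0.88 = 79.5%; at r = 0.2 it is 0.70/0.76 = 92%. Spurious gain 9.5 to 22 points.
- Counting unsubmitted prompts as non-abstinent: both phases give (1 − p)·s. Spurious gain 0.

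**Step 3. Replacement**

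Let q be the share of B positives replaced by a negative repeat (assumed), with every prompt answered. A gives 1 − p; B gives (1 − p) + p·q.

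- p = 0.20: q = 10%, 25%, 50% gives 82%, 85%, 90% in B against 80% in A.
- p = 0.40: the same q gives 64%, 70%, 80% in B against 60% in A.

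A replaced positive looks like an ordinary submitted negative, so the result is the same under either scoring rule.

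**Step 4. A separate effect of voucher value**

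If submission of true negatives rises from an assumed 85% in A to 90% or 95% in B, and missing counts as non-abstinent, the gain is (1 − p) × 0.05 or (1 − p) × 0.10. That is 4 or 8 points at p = 0.20, and 3.5 or 7 points at p = 0.30. This does not come from the submit screen, and automatic logging would not remove it.

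**Step 5. Denominator**

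Scheduled prompts per patient: 14 × 3 = 42, 28 × 3 = 84 and 14 × 3 = 42, in all 168.

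**The case against.** Several objections have force.

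- **Phase B does not pay a patient to hide a positive.** A reader might infer that it does. The voucher schedule says otherwise: withholding earns US $0 more than submitting, because both reset the voucher. What changes is that B drops the US $2 that A pays for disclosure, and rewards a negative repeat. This correction stands.
- **The larger figures need a scoring rule that the article does not state.** A reader might take the 7 to 15 or 9.5 to 22 points as the expected bias. They apply only if unsubmitted samples leave the denominator. The rule may be set in an analysis plan that is not shown, so its absence is no fault, and scoring submitted samples only cannot be presumed.
- **Replacement is limited.** The window is 30 minutes, the voucher needs a reading of 0.00, the Introduction puts breath detection at up to 12 hours, and the facial photo limits substitution by another person. A repeat may also correct a false reading. All this keeps q down, but does not make it zero or equal across phases.
- **Discarded readings may be stored.** The article describes only what happens on submission and is silent on the rest, so loss of these readings is not established.
- **Other checks exist.** Weekly ATFB bypasses the submit button, and the proportion of samples submitted is an outcome. These help interpretation, but neither is the measure by which the article judges feasibility, if that is breath-tested abstinence.

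An appeal to a later analysis plan does not dispose of the point. A scoring rule can close the withholding route, but it cannot identify a replaced positive that was never recorded.

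**Conclusion.** The point holds as a conditional one: submission by a patient who knows the result, combined with payment that differs by phase, can bias the abstinence contrast toward B and can mimic the return to baseline in the second A phase. The document does not support saying that the contrast is biased, or by how much, because p, r and q are not given and cannot be derived from it. Withholding contributes nothing if unsubmitted prompts count as non-abstinent. Replacement contributes under either rule, by p·q, with q limited by the half-hour window. The 3.5 to 8 points for better submission of negatives are a separate matter of voucher value and should not be attributed to the submit screen. The point is worth acting on because it concerns data capture: if discarded readings are not kept, they cannot be recovered at analysis.

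**What to change.** 1. Have the app log every completed reading automatically with a time stamp, in all phases, and store retakes as additional readings. If it already does so, say so.
2. Score each scheduled prompt from the first identity-valid reading in its window.
3. Use all scheduled prompts (42, 84 and 42 per patient) as the denominator, and count prompts with no such reading as non-abstinent.
4. Report submission rates by phase. Give observed-only and ATFB-based analyses as sensitivity checks, because higher voucher values in B may also raise submission of true negatives. Self-report is better kept as a sensitivity check than used to fill in the main breath measure.

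The voucher schedule need not change. The cost is an app change, a sentence in the consent form and a sentence in the outcome definition; the article does not show how large the software work would be. Scoring the first reading also sets aside retakes made for a genuinely faulty result, although these remain in the log and can be examined. Measured abstinence in B may look less favourable.

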### Ecological Momentary Assessment

After the submission of the breathalyzer result, ARMS will prompt the patient to respond to 3 to 5 questions about moods and states that might be pertinent to the patient’s recovery. As shown in Table 2, the ecological momentary assessment (EMA) questions include options that were created based on the Addiction Neuroclinical Assessment (ANA) framework developed by Kwako et al [33,34], which postulates that three domains defined as poor executive functioning (ie, working memory and impulsivity), negative emotionality (eg, depression, anxiety, and symptoms of withdrawal), and incentive salience (eg, thinking about and/or craving alcohol) are the primary factors that cause and maintain addictions [33-37]. Kwako and colleagues [33] propose that ANA domains, assessed by self-reports and cognitive testing, as well as genetic analysis and, eventually, neuroimaging, can be used to identify groups of patients who do not respond to existing treatments. The ANA also provides a framework to guide treatment adaptations to improve outcomes for specific groups (ie, nonresponders or more severe disease groups). Furthermore, it can be used to match individuals to specific interventions based on their ANA characteristics. Thus, the ANA may provide an ideal structure for developing a personalized medicine approach to integrated treatment for AUD.

**Table 2 table2:** Description of the ecological momentary assessment (EMA) questions.

EMA question	Type of response	ANA^a^ domain
Since your last assessment, how much have you craved alcohol?	5-point Likert scale	Reward salience
I want to drink so bad I can almost taste it.	5-point Likert scale	Reward salience
How happy do you feel right now?	5-point Likert scale	Negative emotionality
How sad do you feel right now?	5-point Likert scale	Negative emotionality
How relaxed do you feel right now?	5-point Likert scale	Negative emotionality
How Stressed do you feel right now?	5-point Likert scale	Negative emotionality
How bored do you feel right now?	5-point Likert scale	Negative emotionality
How irritable do you feel right now?	5-point Likert scale	Negative emotionality
In the last two hours have you been doing things without thinking?	5-point Likert scale	Executive functioning
In the last two hours have you been acting on impulse?	5-point Likert scale	Executive functioning
In the last two hours have you felt self-controlled?	5-point Likert scale	Executive functioning

^a^ANA: Addiction Neuroclinical Assessment.

The EMA questions in ARMS will provide clinicians and researchers with relevant real-time information about their patients’ states and moods specific to the three ANA domains. This information may serve multiple purposes. First, comparing the EMA answers and breathalyzer results of the general patient population may assist clinicians in identifying specific traits and states associated with positive or negative treatment outcomes, possibly enabling them to identify, at the beginning of treatment, whether a participant may benefit from more intensive care. Second, and perhaps more important, by comparing the EMA answers and breathalyzer results of a specific patient, clinicians may be able to identify specific cognitions and moods associated with risks of future relapse, enabling them to intervene before relapse occurs.

### Reminders and Messages

To promote compliance and recovery, the ARMS app will send reminders when it is time to submit the breathalyzer samples and EMA responses. It will also send an alert when patients fail to submit a sample. To further enhance treatment response, ARMS will also send reinforcing messages. These messages range from congratulating patients when they reach a certain milestone (eg, “Three straight days of alcohol abstinence, keep up the good work!”) to encouraging them after relapse (eg, “Treatment success is not about falling but how quickly we pick ourselves up” and “Tomorrow you get another chance to do what’s right by you!”). Patients will also receive messages confirming their breathalyzer sample submissions and facial image validations, as well as messages informing them about the number of rewards earned in the contingency management intervention. Figure 1 presents an overall schematic of how ARMS functions.

**Figure 1 figure1:**
[figure not shown]
Data capture and participant flow.

### Redeeming Rewards

Patients will be able to use the ARMS app to redeem the credit earned immediately after the breathalyzer sample is validated. Patients can choose to redeem any specific amount in the form of a digital gift card sent to a preregistered email address. The gift card information will also be stored in both the patient’s and provider’s ARMS interfaces.

### Provider Interface

All data collected in the patient’s mobile ARMS app will be stored securely in a database that can be accessed by providers from the provider dashboard. This web-based console allows providers to register new patients, access and evaluate patient performance, and validate the authenticity of the breathalyzer samples submitted. Furthermore, the provider dashboard provides an easy way for providers to identify patients that may need more personalized care by displaying a summary of the status of all patients enrolled in the system, with nonadherent patients or patients failing to achieve their goals being placed at the top of the list. The ARMS provider interface was also created to integrate directly into electronic medical record systems using standard health information exchange formats, such as Health Level Seven (HL7; a specific method for the exchange, integration, sharing, and retrieval of electronic health information) and Clinical Core Document (which offers updates to previous efforts by HL7), thereby enabling clinicians to receive progress alerts based on nonadherence and overall status. These provider alerts are customizable to accommodate variations in workflow.

### ARMS Contingency Management Intervention

Contingency management interventions involve providing reinforcement (ie, rewards or incentives) after a targeted behavior is exhibited. In the field of substance use disorder treatment, contingency management usually consists of providing vouchers of monetary value after a specific period of substance abstinence is verified through the submission of a negative drug screening sample. The combination of features present in ARMS and the BACtrack breathalyzer device enables the provision of contingency management remotely to any patient that owns a smartphone. To provide more personalized care, the ARMS contingency management intervention is flexible, allowing providers to modify and adjust several components of the intervention. This flexibility allows providers to mold the contingency management intervention to best suit the patient’s specific needs as well as to adapt it to the daily clinic routine.

To initiate the contingency management intervention with ARMS, treatment providers will select the type of response that will be targeted in that intervention (eg, alcohol abstinence and low levels of alcohol use), the schedule of reinforcement (ie, the number of samples to be submitted daily), and the duration of the intervention. After these parameters are set, patients will be prompted by their ARMS app to record and submit their breathalyzer samples at the predetermined times. To reduce the burden or other inconveniences related to sample submission, patients will have a half-hour window to submit each sample following the prompt. After a sample is submitted, patients will receive a message stating that the sample was received and is currently awaiting verification. A research staff member will then have 24 hours to confirm the patient’s identity (based on the facial image captured at the time of sample collection). The research staff member will be presented with a recommendation for approval or rejection based on facial recognition verification. This process will be evaluated for the potential to automate verification. After providers verify the authenticity of the sample, patients will be immediately informed that the sample was verified and, when the target response is achieved (ie, confirmed alcohol abstinence), patients will be notified of the number of rewards earned. If the sample is deemed invalid or the target behavioral response is not accomplished, patients will be notified of the reason they did not earn the reward.

### Buildout Options

There are additional features that are either in progress or are planned for future iterations. One such feature is to enable the selection of different target responses such as abstinence (ie, BAC=0.00) or reduction of heavy drinking (ie, BAC=0.08). We also plan to enable the selection of different options related to specific components of the contingency management intervention; for example, setting the expected number of sample submissions to be fewer than 3 submissions per day, scheduling sample requests at different times of day, or using artificial intelligence to conduct immediate facial recognition after the BAC sample is submitted**.** We also intend to make reminders multimodal so that they can reach users through different means based on their preferences. Users would thus be able set up their reminders as local alarms on their smartphone device or receive them via push, SMS text messages, or automated voice calls.

Another feature that is in progress but will not be active during this phase 1 study is defining patient-specific “hot zones” (and “cold zones”) using a type of geolocation “fence” in an effort to provide patients with feedback and alert them when they are entering a physical area or location where they have not achieved their stated drinking goals (Figure 1). Finally, we plan to develop additional dashboard features, including the ability for patients to see which EMA responses are correlated with alcohol outcomes over time and which factors are most likely associated with craving and alcohol use, to promote additional awareness of executive function and moods associated with relapse.

